### Tolerance to the medication

Donepezil is judged to be fairly well tolerated in older people at the 10 mg/day standard dose regimen. We selected Donepezil for our study since, according to the last Cochrane Review on cholinesterase inhibitors [59], fewer patients suffer adverse events on Donepezil when compared with other cognitive enhancers such as Rivastigmine. The most common reported intolerance is due to gastrointestinal problems such as abdominal pain, anorexia, nausea, vomiting, diarrhoea, and rarely dizziness, headache, and insomnia, which were significantly more frequent in the ChEI than in placebo groups in the referenced meta-analysis. Participants who would develop gastrointestinal intolerance with Donepezil at 10 mg/day will have the dose reduced to 5 mg/day and switched to a bedtime regimen as per current clinical practice. Participants who have persistent intolerance, and anyone who experiences a major adverse reaction, will be withdrawn from the study and the events reported to the Research Ethics Board and to Health Canada.

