### Measurements and Procedures

All participants will undergo a baseline, one month, and a final six-month assessment. Baseline gait assessment will occur within one week prior to starting donepezil (T0), with a second assessment occurring after 4 weeks of treatment at 5 mg of medication (T1). The third and final assessment will occur after participants have been on the full dose of donepezil, 10 mg, for a period of 5 months (T2), yielding a total period of follow-up of 6 months from baseline. Assessments at each of these time-points will include gait analysis, balance sway, and balance confidence as well as cognitive measurement of attention and executive function. Falls will be retrieved by phone interview as has been done in previous studies [47,48]. A timeline for the proposed study can be found in Figure 4.

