### Outcomes measures

#### Primary outcomes

1. Improvements in gait velocity (cm/second) at month six

2. Reduction in gait variability assessed as standard deviation (SD) and coefficient of variation (CoV) at month 6.

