### Statistical Analysis

Analyses will be performed according to an intention-to-treat principle. Baseline characteristics and gait parameters will be descriptively summarized using either means and standard deviations or frequencies and percentages, as appropriate. Comparisons of the changes in the mean balance confidence score will be assessed using *t*-test. The coefficient of variation [CoV = (SD/mean)*100] will be used to quantify gait variability. We will use linear regression to perform between-group comparisons using three data points (baseline, one month, six months) with baseline – 1 mo. corresponding to before treatment and 1 mo. – 6 mo. corresponding to treatment with donepezil. Linear regression models, both unadjusted and adjusted for age, sex, and history of falls, will be used for comparison of individual variables. Using the baseline value of an endpoint as a covariate is more powerful statistically than comparing the differences from baseline. The statistical significance of the results will be determined by Hochberg's variation of the Bonferroni procedure for multiple testing [65]. Two-sided *p *< 0.05 will be considered statistically significant. All calculations will be made using SPSS software package version 16.0 (SPSS Inc., Chicago, IL).

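### Participants with persistent intolerance or a major reaction leave the study, not only the drug, so month-6 outcomes are lost and the intention-to-treat analysis is undermined

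*Protocol article*

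**What the plan says.** Under Tolerance to the medication, the protocol article sets two steps. Participants with gastrointestinal intolerance at the higher dose "will have the dose reduced to 5 mg/day and switched to a bedtime regimen as per current clinical practice"; they remain in the trial. For those whose problem continues, or who have a serious reaction, the rule is: "Participants who have persistent intolerance, and anyone who experiences a major adverse reaction, will be withdrawn from the study". The first step acts on the drug, the second on study participation. The same section says of the listed intolerances that they are events "which were significantly more frequent in the ChEI than in placebo groups in the referenced meta-analysis".

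The Statistical Analysis section states: "Analyses will be performed according to an intention-to-treat principle". The primary outcomes are tied to the final visit: "Improvements in gait velocity (cm/second) at month six" and "Reduction in gait variability assessed as standard deviation (SD) and coefficient of variation (CoV) at month 6". Measurements and Procedures describes that visit (T2) by drug exposure: "The third and final assessment will occur after participants have been on the full dose of donepezil, 10 mg, for a period of 5 months". The article describes no T2 visit for a participant who has stopped the drug. The secondary outcomes include the total number of falls by month 6 and the proportion of participants who fall.

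**The concern.** Intention-to-treat compares everyone randomised, in the arm assigned. That requires outcomes on everyone, or a defensible treatment of those missing. A rule that takes people out of the study because of a reaction to treatment creates missing month-6 outcomes by design, for a reason related to treatment.

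If the rule acts more often in the donepezil arm, the month-6 comparison moves towards donepezil tolerators against placebo participants who were less often removed. The estimate then answers a different question from the one promised. Falls are affected in a second way: a person withdrawn early has fewer months in which a fall can be recorded, so both fall measures can look better in the arm with more withdrawals, without any drug effect.

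**Working it through.** **1. Following the rule through.** Both primary outcomes need a clinic walkway assessment at month 6. A participant withdrawn from the study has no such visit and returns no further calendars. Data up to withdrawal exist; month-6 data do not. An analysis plan can choose how to handle the gap, but it cannot recover outcomes that were not collected.

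**2. The plan's own drop-out figure.** Sample size determination needs 69 per arm for analysis, allows 5% drop-out for both arms together and recruits 75 per arm. 69 / 0.95 = 72.6, so 73; the stated 75 is close. No rate is given by arm or by reason.

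**3. Possible bias (illustration).** Let q be the share of the donepezil arm withdrawn. Assume that tolerators gain the planned 0.10 m/s (10 cm/s), that those withdrawn keep no benefit, that placebo loss is non-selective, and that only observed cases are analysed.

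- Observed-case result = 10 cm/s.
- True intention-to-treat effect = 10 × (1 − q).
- Overstatement = 10 / [10 × (1 − q)] − 1.

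| q (assumed) | True effect, cm/s | Overstatement |
|---|---|---|
| 5% | 9.5 | 5% |
| 10% | 9.0 | 11% |
| 15% | 8.5 | 18% |
| 20% | 8.0 | 25% |

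If those withdrawn would be only 5 cm/s worse than tolerators, the shift halves: 0.05 × 5 = 0.25 cm/s at q = 5% and 0.20 × 5 = 1.0 cm/s at q = 20%. The overstatement is then 10/9.75 to 10/9.0, about 3-11%.

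**4. Power.** No SD is stated. Taking 69 per arm, two-sided 0.05 and 80% power, the implied standardised difference is √(2/69) × (1.960 + 0.842) = 0.477, so SD = 0.10/0.477 = 0.21 m/s. Power = Φ{0.10 / [SD × √(1/n_D + 1/n_P)] − 1.960}, for the 0.10 m/s observed-case difference. Placebo loss is held at 5% (assumed).

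| Recruited per arm | Donepezil n, 5% → 20% loss | Placebo n | Power |
|---|---|---|---|
| 70 (140 in total) | 66.5 → 56 | 66.5 | 78.5% → 74.9% |
| 75 (150 in total) | 71.2 → 60 | 71.2 | 81.2% → 77.7% |

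The cost is about 4 points in either case. Bias is the larger issue.

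**5. Falls and observation time (illustration).** If 15% of the donepezil arm left at month 2 (assumed), the arm would lose 0.15 × 4/6 = 10% of its planned observation time. Its expected fall count would drop by about 10% with no change in the underlying rate.

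**The case against.** The strongest defence is that this is a short safety contingency in a journal article. It does not say in terms that T2 is cancelled. Intention-to-treat concerns analysis by assigned arm, the analysis uses three time points so baseline and one-month data could contribute, and missing-data handling commonly sits in a fuller document. This stands against any claim that the article specifies a completers-only analysis; it does not. It does not remove the point, because the article states a rule and the rule says study. If drug alone was meant, the sentence needs the same correction. Nor do one-month values replace month-6 values: they are obtained at 5 mg after four weeks and say little about a participant's course after stopping.

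A reader might infer more than the documents support:

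- **That mainly donepezil participants will be removed.** The reported excess concerns common intolerances. Withdrawal is triggered by the narrower set that persists or is major, after a dose step that keeps some people in. The rule covers both arms. Greater loss on donepezil is likely, not established.
- **That the analysed numbers must fall below 69 per arm.** At 5% loss this happens with 70 per arm but not with 75 (71 remain; the shortfall starts above 1 − 69/75 = 8%). It comes from the separate conflict between 140 in total and 75 per arm.
- **That these withdrawals come on top of the 5% allowance.** That figure is taken from two six-month drug studies in mild cognitive impairment and may already include stopping for intolerance.
- **That fall or balance harm will be hidden.** The article calls dizziness rare. Effect of Donepezil on balance reports no significant excess of gait disturbance, falls or balance problems on this drug class. Falls before withdrawal are already on the monthly calendars, and the events leading to withdrawal are reported to the ethics board and the regulator. What can be lost is later calendars and the T2 balance assessment.

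**Conclusion.** The point holds in this form: the rule, followed as written, loses month-6 outcomes for a treatment-related reason and so undermines the promised intention-to-treat comparison. The direction of any imbalance is probable from the article's own account of intolerance, but not certain.

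The size is unknown. The 5-25% overstatement depends on all four assumptions in the illustration and is not a forecast. At the plan's own 5% drop-out the shift is 0.5 cm/s on 10, and it is smaller if those who stop keep some benefit. The 20% end is four times the planned rate. If few participants are withdrawn, the consequence is minor. The change is still worth making, because uncollected outcomes cannot be restored at analysis.

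**What to change.** State separately what happens to study drug and what happens to follow-up. Participants who stop study drug for any reason remain in the study for the scheduled T1 and T2 gait, balance and cognitive assessments and for the fall calendars, unless they withdraw consent. All collected data are analysed as randomised, and falls are analysed allowing for each participant's observation time. The description of T2 by time on full dose should be reconciled with this, so that it also covers those on a reduced dose or off drug. The clinical decision on when drug is reduced or stopped is not touched.

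The cost is a sentence or two in the protocol and consent form, and visits that are already scheduled. Some participants who stop will decline to return, so some loss will remain. Including people who stopped may also give a smaller estimated effect than a tolerators-only comparison; that is the effect that intention-to-treat is meant to estimate.

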### Effect of Donepezil on balance

The last Cochrane review and meta-analysis [59,60] on adverse events associated with cholinesterase inhibitors showed that adverse events such as gait disturbances, falls or balance problems are not significantly more frequent in the ChEI groups than in placebo. These findings were pooled evidence from six or more studies in the referenced meta-analysis. In our ongoing pilot project involving 16 participants with early dementia we have not found any participants who experienced adverse events related to balance, bradycardia, or hemodynamic changes. As per clinical practice, participants having bradycardia before randomization (baseline heart rate below 60 beats/minute) will be excluded of the study. Therefore, based on published evidence and our accumulating direct experience, we do not expect a significant negative effect of ChEI in balance and/or hemodynamic changes in our population.

## Discussion

Elderly adults with cognitive problems are one of the most vulnerable sectors of our society with clear mental, social, and physical disadvantages. They are more likely to experience falls, and experience further mobility decline due to having fallen; therefore is an urgent need to identify evidence based interventions for reducing the risk of falls and related injuries in people with cognitive impairment. To date, no adequately- powered studies have investigated the effect of cognitive enhancers to reduce falls in people with MCI. As falls are one of the most common reasons for both hospital admissions and nursing home placements in older adults with cognitive difficulties, they contribute significantly to the overall health care burden for Canada.

This study is distinctive due to the fact the intervention will target cognition with the outcome to improve mobility, balance, gait performance, and risk of falls. If we can demonstrate the effect of cognitive enhancers on fall risk and gait performance, these results will reveal a previously unrecognized benefit of this pharmacological therapy, which could in turn serve to decrease this burden. We are a unique position to conduct this project based on our previous research program expertise with gait assessment as well as our record of research involving elderly people with MCI

By characterizing and understanding the effects of cognitive enhancers on fall risk in older adults with cognitive impairments, we will be able to pave the way for a new approach to fall prevention in this population. This RCT study will provide, for the first time, information regarding the effect of a medication designed to augment cognitive functioning have on the risk of falls in older adults with Mild Cognitive Impairment. We will expect a significant reduction in the risk of falls in this vulnerable population as a function of the reduced gait variability achieved by treatment with cognitive enhancers. In this vein, we would establish that medications that augment cognitive function could be a complementary therapeutic option for reducing fall risk in people with MCI. This may contribute to a new approach to prevent and treat fall risk in this population, which will lead to improving the autonomy and quality of life of seniors in early stage of dementia.
